### Stress-regulation tasks (neurocognitive assessments)

We assess these four domains of stress regulation (Fig. 2; exogenous-explicit, exogenous-implicit, endogenous-explicit, and endogenous-implicit) using different outcome measures: self-report, behaviour, physiology, and brain imaging. Self-report questionnaires are used to assess perceived stress (e.g., subjective fear ratings). These are acquired via Expyriment [53], the software we use to present task stimuli, along with assessments of behavioural responses (e.g., reaction time, response accuracy) recorded during stress regulation tasks. Physiological response assessments of autonomic nervous system measures (e.g., skin conductance, heart rate, and pupil size) are used to measure affective responses to stressors using BrainVision Recorder (Brain Products; Gliching, Germany) and Eyelink-1000 Plus eye-tracker (SR Research, Ottawa, Canada). We additionally use brain imaging to assess brain activity and connectivity within and between large-scale brain networks using a Siemens Skyra 3 T MR system (Siemens, Erlangen, Germany). In addition, we record respiration via BrainVision Recorder (Brain Products; Gliching, Germany) during the neurocognitive tasks to correct the MR images for physiological noise. Saliva samples are acquired while performing the tasks to measure salivary cortisol levels as a response to stressors using salivette cotton swab tubes (SARSTEDT, Numbrecht, Germany).

**Fig. 2 Fig2:**
[figure not shown]
Experimental design for each of the tasks residing in four domains of stress regulation (implicit-exogenous, explicit-exogenous, implicit-endogenous, and explicit-endogenous) with example stimuli. **A** An image of a room is shown on the screen as the context. Shortly after, a shape (e.g. circle or square) is shown within the room providing information on how likely it is to receive an electrical stimulation on the hand. During the conditioning phase, electrical stimulations are administered at the end of 35% of trials depicting one of the shapes. The other shape is never paired with an electrical stimulation. In the remaining phases of the task the same stimuli are shown but electrical stimulations are never administered. **B** Participants select the emotion depicted on a face (happy or scared) while ignoring the word describing an emotion (happy or scared; “blij” or “bang” in Dutch) superimposed on top of the face. The word can either match the emotion on the face (congruent trial) or not (incongruent trial). Depicted stimuli [61] are examples; actual stimuli will be taken from Ekman and Friesen. **C** Participants fixate their gaze on a fixation cross for 5 min during a resting state scan. A stress induction procedure follows, including a socially evaluated cold pressor test and a mental arithmetic task. Another 5-min resting state scan is acquired after the stress induction procedure. **D** Participants are asked to make the grey disk larger or smaller using only mental strategies. After a short rest they see the size of the disk change, reflecting their brain activity during their regulation period. This serves as feedback which can be used to learn and improve one’s strategies to control their brain activity

#### Implicit, exogenous stress-regulation – fear conditioning and extinction task

Implicit, exogenous stress regulation is assessed using a differential fear conditioning and extinction paradigm in the MRI scanner, since this task involves measuring spontaneous responses to an external stressor. Mild electrical stimulation to the fingers is used as the unconditioned stimulus (US). Two shapes are used as conditioned stimuli (CS), and they are presented for 4 s on top of a specific background image (the same for both stimuli) with an average intertrial interval of 12 s. One of the two shapes is sometimes paired with a US during the final 200 ms of the stimulus presentation (CS +) and the other one is never paired with the US (CS-). Reinforcement rate using the US is set at 35%. After fear conditioning has occurred, we proceed with a fear extinction task inside the MRI scanner. The two CS are presented as described in the previous paragraph, however the CS + is not paired with the US anymore. Furthermore, the background image is changed, representing a different context during extinction learning. On the following day, an extinction recall task is performed outside of the scanner, in order to assess the strength of the extinguished memory. The background image is the same as during fear extinction and the CS + and CS- are presented without the administration of electrical stimulations (i.e., the US). A fear renewal task follows, to assess the strength of the fear memory in the context it was acquired in. The background image is therefore the same as the one used during the fear conditioning task. The CS + and CS- are presented as described in the fear conditioning task, however without administration of electrical stimulations.

#### Explicit, exogenous stress-regulation – emotional conflict resolution task

We will explore explicit, exogenous regulation by assessing behavioural responses and brain activity during a Stroop-like emotional conflict resolution task as described by Etkin et al. (2006). This task requires explicit attentional control and response inhibition over emotional processing that arises from conflicting external emotional information. The task consists of 148 presentations of happy or fearful facial expression photographs chosen from the set of Ekman and Friesen (1976). Faces are cropped and the words ‘‘FEARFUL’’ or ‘‘HAPPY’’ are written across the face in Dutch (i.e. “BANG”, “BLIJ”), such that word and expression are either congruent or incongruent. Stimuli are presented for 1 s, with a varying interstimulus interval of 3–5 s, during which a central fixation cross is shown. Participants are instructed to respond as fast and accurately as possible, by selecting the response buttons corresponding to ‘‘fearful’’ or ‘‘happy’’ for the expression on the face. This task is designed to probe emotional conflicts by manipulating the congruency of the stimuli. Congruency refers to whether the two types of stimuli shown simultaneously in this experiment (i.e., facial expression and written word) match or not. For example, when a facial expression matches the word superimposed on it is considered a congruent trial, and when the facial expression does not match the word superimposed on it is considered an incongruent trial.

#### Implicit, endogenous stress-regulation – resting under stress

We will assess resting-state functional connectivity within and between large-scale brain networks (ECN, SN, DMN) before and after a stress induction task, in order to investigate implicit, endogenous stress regulation. This task is chosen since it involves measuring spontaneous brain activity that is driven by an internal stressful state following a stress induction. Participants first undergo a resting state fMRI scan, for which they are instructed to keep their eyes open and fixated on a fixation cross on the screen. They are instructed to let their mind wander, without thinking of anything specific, or performing any repetitive mental activities. Shortly after this scan, a stress induction procedure takes place. The procedure is a modified version of the socially evaluated cold pressor test (SECPT), during which a researcher unknown to the participant will enter the MRI lab to perform the stress induction tasks. The researcher asks the participant to immerse their foot in a box of cold water (1.8–2.2 ^o^ C) and try to keep it in for 3 min. The researcher then tells the participant that they are evaluating their facial expressions during the task. The researcher is instructed to abstain from giving positive feedback at all times and to try to keep a neutral facial expression. Once the Cold Pressor Test is over, the participants foot is covered with a towel and the researcher continues with the second part of the stress induction. In this part the participant has to count backwards, in steps of 17 or 13 from the number 1872, or 2013 respectively. The researcher asks them to be as fast and as accurate as possible. If they are too slow the researcher asks them to speed up. If they are incorrect the researcher asks them to start from the beginning. This task also lasts 3 min. After stress induction, a second resting-state fMRI scan is acquired, with the same instructions as before.

#### Explicit, endogenous stress-regulation – self-regulation of brain networks under stress

A real-time fMRI neurofeedback paradigm, that has been recently developed and tested [54] is used to assess endogenous, explicit stress regulation after the previously described SECPT procedure. This task was selected as it requires active regulation of brain networks as a response to an internal stressful state. This task takes place after the SECPT and a resting state scan, well within the acute stress phase of the preceding stress induction. The stimulus used for neurofeedback presentation is a circle with a grey disc covering half of its area. Participants are asked to always fixate at the dot in the centre of the circle. During “Rest” the colour of the dot is black, and participants are instructed to rest, and think of nothing specific. During “Regulation” the dot is green, and arrows are pointing towards the outer circle or towards the centre of the circle, and participants are asked to perform the regulation task described below. The participants are instructed to control their brain activity, in order to change the size of the disc on the screen. They are told that they could do this by thinking of something specific, performing some mental task internally, or getting into a certain mood, emotion, feeling, or state of mind. Participants are also instructed to try to avoid movement, including facial movements, limb movements and irregular breathing patterns. During “Feedback” the colour of the dot is orange, and the size of the grey disc will change reflecting the participant’s performance on the preceding regulation trial. The size of the disc directly reflects activity balance between the SN and ECN, therefore participants will have to learn for instance that increasing the size of the circle is possible by shifting the balance towards SN, while decreasing it is possible by shifting the balance towards ECN. Network balance is operationalised as the difference of the averaged activity of each of these two networks.

### Ecological Momentary Assessments (EMA)

The EMA consists of 6 days in which 6 surveys are filled throughout the day assessing mood, subjective stress levels, event appraisal, in combination with physiological monitoring for signs of stress [55, 56]. On all days of the week, participants are expected to fill in 6 short questionnaires on a smartphone app (SEMA3: http://www.sema3.com, Melbourne, Australia) that take maximally 3 min each to fill in. The first questionnaire of the day will additionally have questions regarding sleep quality, while the last will have items of self-reflection regarding the previous and the upcoming day. Additionally, during this week participants will wear an E4 wristband (Empatica sarl, Milano, Italy) measuring skin conductance, heart rate, skin temperature, and movement.

### Procedures

#### Recruitment

We recruit students via flyers on university campus sites, study advisors’ offices, student associations, and social media groups. Flyers will point students to our website which contains a more detailed description of our study and some necessary information for the procedures that we use. Interested individuals will find a link to a screening survey implemented on a platform specialised for anonymous recruitment of participants for scientific research (https://www.soscisurvey.de). On this website, potential participants are asked to answer questions pertaining to the exclusion criteria described earlier, as well as the Perceived Stress Scale questionnaire. Personal information and questionnaire scores are not accessible to the researchers. If all inclusion criteria and none of the exclusion criteria are met, potential participants are prompted to contact us. Thus, we are able to approach a large number of students and perform a pre-screening procedure that ensures their privacy. Once a potential participant contacts us, they receive detailed information about our study via email, and an appointment is scheduled. During this meeting, exclusion criteria are again checked, all measures, tasks, and procedures of the study are discussed, and an informed consent form is signed. Once participants join the study measurement sessions are planned, and participants receive regular email reminders to safeguard completion of the assessments and participant retention.

#### Baseline measurements

After inclusion, the participant’s baseline measurements are acquired. First, two visits (on consecutive days) at the Donders Centre for Cognitive Neuroimaging (DCCN) are scheduled. On the first visit participants are asked to perform some of the neurocognitive assessments (Fear Conditioning task, Emotional Conflict Resolution task, and Resting State fMRI task). On the second visit participants are asked to perform a short task, part of the Fear Conditioning task. In addition, they undergo clinical assessments in the form of questionnaires on both days. Participants will then follow a week of ecological momentary assessments, during which they are asked to answer multiple short questionnaires during their daily life. After these baseline measurements, participants are randomly assigned to two groups as described earlier.

#### Intervention

Participants in the MBSR group receive the MBSR training and their attendance is logged, while participants in the wait-list group will not receive any planned intervention or measurements for the corresponding 8 weeks.

#### Post-intervention

As soon as the MBSR training has concluded, all participants are asked to visit the DCCN for their post-treatment measurements. These visits (visit 3 & 4) are scheduled on consecutive days and will involve the same neurocognitive and clinical assessments as the baseline measurements, with the addition of the Real-time fMRI Neurofeedback task. In addition, another ecological momentary assessment week is planned.

#### Follow-up

Two months later, during visit 5, clinical assessments are planned as a follow-up measurement. Participants in the wait-list group will then be able to receive the MBSR training, after which they are asked to visit the DCCN for a last clinical assessment.

### Statistical analysis

#### Sample size calculation

The sample size, which is reported on http://trialregister.gov, was calculated on the basis of our planned Analysis of Covariance (ANCOVA) to estimate the difference between groups in perceived stress at post-treatment, while taking into account individual baseline measurements of perceived stress as a covariate. We use the method of Borm, Fransen, & Lemmens (2007), which adjusts the sample size calculated for an independent sample t-test by multiplying with the factor (1-r^2), where r is the correlation coefficient between baseline and post-treatment measurement. We aim to achieve a power of 80% with an *α* = 0.05. The correlation between baseline and end-of-treatment perceived stress is estimated at *r* = 0.7, based on data from Verweij et al. (2018). Assuming a moderate effect size of Cohen's *d* = 0.4, as reported by a large RCT on a general student sample (Galante et al., 2018), we would need 54 participants per group. Taking also into account an average attrition rate (10%) of studies on student populations reported in a meta-analysis by Khoury et al. (2015), we aim to recruit a total of 60 participants per group.

Notably, this estimate is conservative. We purposefully focused on one of the latest studies with a student population. The meta-analysis by Khoury et al. (2015) reports a higher combined effect size (*d* = 0.47) in 9 randomised controlled trials of student populations, on measures of stress, anxiety, depression, etc. This would result in our trial achieving a power of 91%. Additionally, this meta-analysis also suggests that the effect size of the treatment effect on different measures of perceived stress specifically is considerably higher than when combined with other outcomes mentioned above. The combined effect size estimate from nine studies on various healthy populations is *d* = 0.74, which would lead to a power of 99% in our trial. Sample size estimations based on the outcomes of our stress regulation tasks have proven to be exceptionally difficult due to the paucity of studies looking at the effects of MBSR on these specific tasks. However, there are indications that the influence of MBSR on some of these tasks is higher than the effect on clinical outcomes. For instance, large effect sizes are reported on extinction retention, the primary outcome of the fear conditioning and extinction task (*d* = 0.93–1.15) [57, 58]. Studies assessing the effects of MBSR on resting state fMRI connectivity between regions within our networks of interest have reported a wide range of effect sizes (*d* = 0.28–0.92) [59, 60]. Therefore, we expect to be able to detect effects of MBSR on these tasks with a well powered study based on our clinical outcomes.

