### Update

We are currently in the process of recruiting and testing participants since April 2021. It is expected that reaching the total sample size which was reported on trialregister.gov will be a challenge. One of the main factors contributing to this is the impact of the COVID-19 pandemic lockdowns, since during the first year of recruitment students were largely studying remotely. In order to address this issue, the study’s recruitment period has been extended by a year, and recruitment efforts have been reassessed. However, there is reason to believe that our sample size estimate is very conservative. The meta-analysis by Khoury et al. (2015) suggests that the combined effect size from studies investigating MBSR on student populations is higher than our original estimate. They report even higher combined effect size on stress measures in studies with various healthy populations, including students. This suggests that our trial is better powered than initially thought. In addition, effect sizes reported in studies investigating the effects of MBSR on stress regulation tasks, similar to the ones we deploy, suggest that the current trial will be well powered to detect these effects [57–60]. This makes us confident that we will be able to detect differences in perceived stress and our stress regulation tasks despite potentially reaching a smaller sample size.

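### The claim that the task outcomes are well powered, even with a smaller sample, fails for the lower part of the cited connectivity range; for PSS it needs an effect above the planned d = 0.4

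*Protocol article*

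**What the plan says.** Protocol article, Sample size calculation. The trial is sized on the PSS ANCOVA: "We aim to achieve a power of 80% with an *α* = 0.05"; "The correlation between baseline and end-of-treatment perceived stress is estimated at *r* = 0.7"; "Assuming a moderate effect size of Cohen's *d* = 0.4". From these inputs, "we would need 54 participants per group", raised to 60 for 10% attrition.

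The same section says that sizing on the task outcomes was very difficult. It cites d = 0.93–1.15 for extinction retention. For resting-state connectivity, it says that studies "have reported a wide range of effect sizes", namely d = 0.28–0.92. It concludes: "Therefore, we expect to be able to detect effects of MBSR on these tasks with a well powered study based on our clinical outcomes".

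Protocol article, Update. Recruitment to target is expected to be a challenge. The section calls the sample size estimate very conservative and points to larger meta-analytic effects. It says the trial will be well powered for the task effects, citing references 57–60, which include the source of the 0.28–0.92 range. It is confident that "we will be able to detect differences in perceived stress and our stress regulation tasks despite potentially reaching a smaller sample size". It gives no reduced sample size, no power at a reduced size and no power for any task outcome.

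**The concern.** The conclusion about the tasks is drawn from a list of effect sizes that runs down to d = 0.28. A trial that needs 54 per group for d = 0.4, with the help of a baseline correlation of 0.7, cannot be expected to be well powered for d = 0.28 on an outcome with no stated correlation. The Update then says that fewer participants would not matter, for PSS or for the tasks, without a figure.

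The effect of MBSR on stress regulation and the role of the large-scale networks are two of the trial's four aims. If a connectivity comparison is null after the trial has been described as well powered, the description invites a reading of no effect. At the low end of the cited range, the trial would miss a true effect about half the time or more. A recruitment shortfall could likewise be reported as harmless on the strength of a statement that depends on which effect size is assumed.

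**Working it through.** **Inputs.** From Sample size calculation: α = 0.05, target power 80%, PSS d = 0.4, r = 0.7 (so 1 − r² = 0.51), 54 analysed per group, d = 0.47 and d = 0.74 as alternative PSS effects, d = 0.93–1.15 (extinction retention), d = 0.28–0.92 (resting-state connectivity). Assumed: a two-sided test (not stated) and, for task outcomes, r = 0.3, 0.5 and 0.7 (none is given).

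**Formula.** Two-sided noncentral-t power with noncentrality (d/√V) × √(n/2). V = 1 for an unadjusted post-treatment comparison, 1 − r² for ANCOVA, and 2(1 − r) for a group-by-time contrast over two time points.

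**Step 1: the plan's own figures.** A t-test at d = 0.4 needs 100 per group, and 100 × 0.51 = 51. Exact ANCOVA gives 52. The stated 54 is slightly higher, and its power is 82%. Attrition: 54 / 0.9 = 60, as stated. At 54 per group, d = 0.47 gives 92.3% (stated 91%; 51 per group gives 90.8%), and d = 0.74 gives over 99% (stated 99%). The figures reproduce closely.

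**Step 2: task outcomes at 54 per group.** For d = 0.28 unadjusted, the noncentrality is 0.28 × √27 = 1.455, and power is 30%.

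| d = 0.28, n = 54 per group | r = 0.3 | r = 0.5 | r = 0.7 |
|---|---|---|---|
| Group by time (the test named under MRI analysis) | 23% | 30% | 46% |
| ANCOVA | 33% | 38% | 52% |

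For 80% power at d = 0.28 without adjustment, 202 per group are needed. With fewer analysed, unadjusted power falls to 26% at 45 and 24% at 40 per group.

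**Step 3: where the claim starts to hold.** Unadjusted, 54 per group gives 79% power at d = 0.54, 81% at d = 0.55 and 87% at d = 0.60. A group-by-time test at r = 0.5 has V = 1 and the same threshold. Scaling 0.54 by √V, the group-by-time threshold is 0.54 × √1.4 = 0.64 at r = 0.3 and 0.54 × √0.6 = 0.42 at r = 0.7. For ANCOVA at r = 0.7 it is 0.54 × √0.51 = 0.39. None reaches 0.28. At d = 0.92, 0.93 and 1.15, unadjusted power exceeds 99%.

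**Step 4: PSS with fewer analysed (ANCOVA, r = 0.7).**

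| Per group | d = 0.4 | d = 0.47 |
|---|---|---|
| 54 | 82% | 92% |
| 51 | 80% | 91% |
| 50 | 79% | 90% |
| 45 | 75% | 87% |
| 40 | 70% | 83% |
| 38 | 67% | 81% |
| 35 | 64% | 77% |

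**Step 5: the remaining tasks.** For the emotional Stroop and neurofeedback tasks the article cites no effect size, so nothing in it supports a power statement for them. The neurofeedback task is added only after treatment (Post-intervention) and has no baseline to adjust for, so the unadjusted threshold of about d = 0.55 is the relevant one if each participant contributes one summary value.

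**The case against.** The strongest defence has four parts.

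- **The task passage is hedged.** It admits that evidence is sparse, says some tasks may show larger effects, calls the connectivity range wide, and speaks of expectation. This softens the Sample size calculation text, but not the Update, which says without qualification that the trial will be well powered for the effects in the cited studies.
- **d = 0.28 is the worst endpoint.** At the midpoint of the range, d = 0.60, unadjusted power is 87%. A reader might infer that the tasks as a group are underpowered. The documents do not support that: extinction retention, the main outcome of its task, is well covered, and so is the upper part of the connectivity range.
- **The Update argues openly from larger effects.** It does not say that power holds at d = 0.4, and the Sample size calculation section gives the size and population of each larger effect. On that premise the PSS claim is right over a wide range: d = 0.47 keeps 80% power down to about 38 per group and d = 0.74 down to about 16. A reader might infer that any shortfall takes PSS below 80%. It does not, because even at d = 0.4 power is about 80% at 51 per group. What stands is that the confidence is stated without its condition.
- **The task correlations are assumed.** How the cited d = 0.28 was defined is also not given. This stands as a limit on the exact figures, but no correlation in the assumed range brings power at d = 0.28 above 52%.

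A reader might also take 54 against 51–52 per group as a material error. It is a small difference on the safe side.

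**Conclusion.** The point holds in limited form. The article attributes adequate power to the full set of cited task effects, and its own lower connectivity figure contradicts this: about 30% power unadjusted at d = 0.28 with 54 per group, and 23–52% across the tests and correlations considered. The claim is sound for extinction retention and for connectivity effects of about d = 0.55 or more, and it has no stated basis for the emotional Stroop and neurofeedback tasks. The d = 0.55 limit is for an unadjusted comparison, or group by time at r = 0.5; it moves between about 0.39 and 0.64 under the other assumptions.

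For PSS, the smaller-sample statement is conditional. At the planned d = 0.4 there is room for about three fewer per group before power drops below 80%. Beyond that, the claim needs an effect larger than planned. The documents do not show that the larger effects are wrong or that the trial is underpowered for PSS as designed. All figures assume a two-sided 5% test.

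**What to change.** Change the text in three places.

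1. Sample size calculation and Update: limit the well-powered statement to effects of about d = 0.55 or more at 54 per group, with the test and correlation assumed. Say that smaller connectivity effects are not powered, so null results there are inconclusive. Note that no effect size was available for the emotional Stroop and neurofeedback tasks.
2. Update: replace the unconditional confidence by PSS power at d = 0.4 and at d = 0.47 for the number actually analysed, as in the second table above.
3. Minor: state that the cited formula gives 51 per group (52 by exact ANCOVA) and that 54 gives 82% power.

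The cost is wording only. Design, analyses and recruitment target are untouched, but the power figures that replace the general claims will look less favourable.
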